Anesthesia is maintained with 1.5–2.0 minimum alveolar concentration (MAC) of sevoflurane and 50% oxygen, with a BIS target range of 40–60. No nitrous oxide is used. At the end of the surgery, inhalation agents are discontinued, and 100% oxygen at 6 L/min is administered. Pyridostigmine and glycopyrrolate mixtures are administered to antagonize the neuromuscular blockade in the MR group, whereas the same dose of saline is administered in the Saline group. All patients are given prophylactic antiemetics with dexamethasone 0.2 mg/kg and ondansetron 0.1 mg/kg. The LMA is removed after the patient begins to breathe regularly. Prior to removal, the LMA cuff is deflated, and any oral secretions are gently suctioned. Careful observation, with supplemental 100% oxygen through a facial mask, is carried out for approximately 5 min after the LMA removal. During this period, an attending anesthesiologist needs to be prepared for desaturation or apnea. The patient is then delivered to the PACU and kept under close observation by the anesthesiologist.

### Measurements

The primary outcome measurement is the oropharyngeal leak pressure (OLP) at a fixed gas flow of 3 L/min just before the start of surgery. Secondary outcomes are intubation time for successful insertion, ease of insertion and mask bagging, intubation attempts for successful insertion, successful insertion rate on the first attempt, hemodynamic parameter changes before and after the insertion, ventilator parameter changes such as peak inspiratory pressure (PIP) and expiratory tidal volume to set tidal volume ratio (TVe/TVs) before and at the end of surgery, the fiberoptic view of the LMA position after the successful insertion, as well as postoperative complications. Other outcomes include extubation time, eye opening time, Watcha agitation score, the Face, Legs, Activity, Cry, and Consolability (FLACC) score during the PACU stay, the amount of analgesics administered during the PACU stay, and duration of the PACU stay.

The modified Yale Preoperative Anxiety Scale (mYPAS) is checked when the patients arrive at the preoperative waiting room with their parents before the premedication [14]. The OLP is determined by closing the expiratory valve at a fixed gas flow and then recording the airway pressure indicated by the anesthesia machine at which an audible gas leak is detected in the mouth [15]. Intubation time for successful insertion is measured from the time of opening the mouth until the time of bilateral chest auscultation and detection of capnography. The insertion attempt is stopped and mask bagging is applied when oxygen saturation falls below 90%. Failure of insertion is defined as the unsuccessful insertion of the device after three attempts. In this case, 0.3 mg/kg rescue rocuronium is administered, and another attempt to insert the LMA is made after 2 min. If an additional attempt is not possible, we will intubate the tracheal tube using direct laryngoscopy. Ease of insertion and mask bagging is subjectively graded by the investigator him/herself as easy, moderate, or difficult. Hemodynamic parameters such as the mean blood pressure and heart rate are recorded before and after the insertion. After fixation of the LMA by taping the tube over the chin, a 3.1-mm fiberoptic bronchoscope (PortalView® LF-DP; Olympus Medical Systems Co., Tokyo, Japan) is introduced just proximal to the end of the ventilator conduit, and the laryngeal view is evaluated according to the method described by Timmermann and colleagues [16]. An optimal view is defined as follows: the tip of the LMA placed behind the arytenoids, the epiglottis is visible, not folded down and not covering the airway, and the vocal cords are completely visible under the epiglottis. Any condition present that falls outside of these criteria is judged as a suboptimal position. At the end of the surgery, end-tidal sevoflurane concentration (ET sevo%), BIS, and train of four (TOF) ratio are recorded. Extubation time is defined as the time from the end of the surgery until the time of removal of the device.

Upon admission to the PACU, agitation and pain scores are measured every 10 min until discharge. Agitation is measured by the Watcha scale, which consists of four possible scores: 1, calm; 2, crying but can be consoled; 3, crying and cannot be consoled; 4, agitated and thrashing around [17]. Pain is measured by FLACC scores ranging from 0 to 15 [18]. If the Watcha score is > 2, FLACC score is > 4, or the patient wants analgesics, fentanyl 0.5 mcg/kg will be administered. This dose can be repeated if the symptoms do not subside, or ketorolac tromethamine 0.5 mg/kg can be administered.

Postoperative complications such as respiratory adverse events (coughing, laryngospasm, bronchospasm, postoperative stridor, and desaturation; SpO_2_ < 95%) [19], gastric insufflation, excessive secretion, postoperative nausea and vomiting, sore throat, and bloody tinge on the LMA surface are recorded. Coughing is defined as persistent coughing lasting more than 10 s. The severity of sore throat is classified using a four-point scale as follows: none, no sore throat; mild, complained of sore throat only upon inquiry; moderate, complained of sore throat without inquiry; severe, change of voice or hoarseness associated with throat pain [20].

The patients are discharged when they are calm and meet a modified Aldrete score ≥ 9 [21], and the duration of the PACU stay is recorded as the PACU stay time.

### Sample size

The primary outcome is the OLP. Just as in our study, a previous study confirmed the successful insertion of LMA as a sealing pressure (OLP) > 15 cmH_2_O [8]. We thought that a risk difference of 10% of this minimal sealing pressure would be appropriate to show the non-inferiority of non-MR group over MR group based on our clinical judgement. Therefore, we set the non-inferiority margin to 1.5. A sample size of 58 in each group is needed to achieve 80% power with an alpha of 0.025 to detect non-inferiority. The data are drawn from our pilot study with standard deviations (SDs) of 3.0 and 2.7. Anticipating a 10% dropout rate, we plan to enroll a total of 64 patients per group. The sample size is calculated using PASS software (version 15.0, NCSS, Kaysville, UT, USA).

### Statistical analysis

Both intention-to-treat and per-protocol analyses will be performed. After testing the normality assumption using the Kolmogorov-Smirnov test, continuous variables will be expressed as the mean and the SD or the median and the interquartile range (IQR). Categorical variables will be expressed as numbers of patients and proportions.

The primary outcome (OLP) will be compared with a non-inferiority analysis. The non-inferiority of the LMA insertion without muscle relaxants (T, test) over the LMA insertion with muscle relaxant (C, active comparator) will be accepted if the upper bound of the two-sided 95% confidence interval for C-T is less than the assumed non-inferiority margin of 1.5. For secondary outcomes, continuous variables will be examined with an independent samples *t* test or the Mann-Whitney *U* test, and categorical variables will be examined with Pearson’s chi-squared test or Fisher’s exact test. All tests are two-sided, and *P* < 0.05 is considered statistically significant. A statistician who was not involved in data collection will conduct all statistical analyses using SPSS software (version 19.0, SPSS Inc., IBM, Chicago, IL, USA).

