## Background

The use of a laryngeal mask airway (LMA) is increasing in pediatric anesthesia, because it provides less direct mechanical stimulation of the airway since it is placed above the larynx. Several studies have compared the insertion of an LMA and a tracheal tube and showed a significantly increased incidence of perioperative respiratory complications when using the tracheal tube in children [1–3]. However, LMA insertion can be more difficult in children than in adults. The unique features of the pediatric airway, including a larger tongue, a larger and floppier epiglottis, a more cephalad and anteriorly located  larynx, a more acute angle of the posterior pharyngeal wall to the floor of the mouth than in adults, and tonsillar hypertrophy may interfere with the ideal positioning of an LMA [4–7].

Neuromuscular blocking agents, also called muscle relaxants, have long been used to facilitate the insertion of airway devices. There are pros and cons, however, for the efficacy of muscle relaxants in LMA insertion. Recently, several studies have reported that muscle relaxants may facilitate the insertion of LMAs by enabling higher successful insertion rates, higher sealing pressure, lower leakage volume, and lower difficulty of insertion in anesthetized adult patients [8–10]. Conversely, Chen and colleagues showed that sealing pressure, airway pressure, insertion rates, and sore throats did not differ based on muscle relaxant administration [11]. However, these studies were all conducted in adult populations, and there has been a lack of evidence as to whether the muscle relaxants can be helpful in facilitating the insertion of an LMA in children. Therefore, we designed this randomized controlled study to test the hypothesis that the ease of insertion of an LMA would not be compromised in children without muscle relaxants compared to those given muscle relaxants prior to insertion.

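### Minor: the rule for categorical secondary outcomes ignores the order of the grades for ease of insertion, ease of mask bagging and sore throat; an ordinal test is a cheap improvement

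*Protocol article*

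**What the plan says.** The Statistical analysis section divides secondary outcomes into two classes. For one, "continuous variables will be examined with an independent samples *t* test or the Mann-Whitney *U* test". For the other, "categorical variables will be examined with Pearson’s chi-squared test or Fisher’s exact test". The same section summarises continuous variables by mean and SD or median and IQR after a normality test, and categorical variables by counts and proportions. It adds: "All tests are two-sided, and *P* < 0.05 is considered statistically significant". No trend test or ordinal model is named.

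The Measurements section defines the graded outcomes. "Ease of insertion and mask bagging is subjectively graded by the investigator him/herself as easy, moderate, or difficult". For the complication list, "The severity of sore throat is classified using a four-point scale as follows", with verbal grades running from none to severe. Ease of insertion and of mask bagging is a listed secondary outcome; sore throat is one of several postoperative complications.

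The Background states the hypothesis that "the ease of insertion of an LMA would not be compromised in children without muscle relaxants". The endpoint on which the trial is sized is different: "The primary outcome measurement is the oropharyngeal leak pressure (OLP) at a fixed gas flow of 3 L/min".

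**The concern.** The grades are ordered, and the question asked of them has a direction: is insertion or mask bagging harder, or sore throat worse, in one arm than in the other? Pearson's test on a two-arm table spends 2 degrees of freedom on three grades and 3 on four, and gives the same answer if the grade labels are permuted. Fisher's exact test on such a table ignores order too. A steady drift towards the worse grades is therefore tested less sharply than it could be, and neither test yields a directional effect estimate.

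Ease of insertion deserves some care because it is the outcome named in the hypothesis. All three outcomes are secondary and none has a planned power, so what is at stake is sensitivity, not validity.

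**Working it through.** **1. The plan's own figure.** The Sample size section gives SDs of 3.0 and 2.7, a margin of 1.5, alpha 0.025 and 80% power. The mean variance is (3.0² + 2.7²)/2 = 8.145, so SD = 2.854. With a true difference of 0, n = 2 × 8.145 × (1.960 + 0.842)² / 1.5² = 56.8, i.e. 57 per arm by the normal formula. With the noncentral t distribution, power is 0.794 at 57 and 0.801 at 58, so the stated 58 is reproduced. Then 58 × 1.10 = 63.8, i.e. 64. This calculation concerns leak pressure only; no figure is given for any graded outcome.

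**2. Which rule applies.** The grades are words without numerical values. A mean with SD, a median with IQR or a normality test does not suit them; counts and proportions do. That places them in the categorical class. This is an inference from the two-class rule, since the article does not assign them.

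**3. Power under an ordered shift.** The article gives no category rates, so a range of baselines was assumed. The other arm was obtained by multiplying every cumulative odds by a common odds ratio (OR). Example: 80/15/5% has cumulative proportions 0.80 and 0.95, hence odds 4 and 19. With OR 0.5 these become 2 and 9.5, i.e. 0.667 and 0.905, which gives 66.7/23.8/9.5%. Each scenario had 20,000 simulated trials at two-sided alpha 0.05. Cells show power as Pearson chi-squared / tie-corrected Mann-Whitney.

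58 per arm:

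| Assumed baseline, % | OR 0.5 | OR 0.4 | OR 0.33 |
|---|---|---|---|
| Ease 80/15/5 | 0.287 / 0.370 | 0.492 / 0.602 | 0.687 / 0.783 |
| Ease 70/20/10 | 0.359 / 0.455 | 0.596 / 0.696 | 0.779 / 0.857 |
| Ease 60/30/10 | 0.392 / 0.494 | 0.624 / 0.728 | 0.798 / 0.875 |
| Sore throat 70/20/8/2 | 0.291 / 0.453 | 0.512 / 0.699 | 0.711 / 0.856 |
| Sore throat 85/10/4/1 | 0.185 / 0.315 | 0.346 / 0.530 | 0.523 / 0.714 |

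64 per arm:

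| Assumed baseline, % | OR 0.5 | OR 0.4 | OR 0.33 |
|---|---|---|---|
| Ease 80/15/5 | 0.315 / 0.406 | 0.535 / 0.645 | 0.730 / 0.820 |
| Ease 70/20/10 | 0.383 / 0.486 | 0.636 / 0.738 | 0.815 / 0.889 |
| Ease 60/30/10 | 0.433 / 0.536 | 0.682 / 0.775 | 0.846 / 0.907 |
| Sore throat 70/20/8/2 | 0.327 / 0.490 | 0.561 / 0.743 | 0.756 / 0.889 |
| Sore throat 85/10/4/1 | 0.206 / 0.344 | 0.379 / 0.568 | 0.577 / 0.757 |

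With three grades the difference runs from 0.907 − 0.846 = 0.061 to 0.602 − 0.492 = 0.110. With four grades it runs from 0.315 − 0.185 = 0.130 to 0.714 − 0.523 = 0.191.

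**4. Type I error.** With no difference between arms, chi-squared rejected in 3.2% to 5.2% of trials and Mann-Whitney in 4.7% to 5.2%. Both are valid. The lowest chi-squared values (3.2% to 3.8%) occur in the sparse four-grade tables, so part of the gap there is conservatism. Fisher's test was not simulated.

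**5. Patterns without a consistent shift** (64 per arm, assumed rates).
- Ease 80/15/5 against 62/33/5, a move from the best to the middle grade only: 58% for chi-squared, 56% to 57% for Mann-Whitney. No gain.
- Ease 75/20/5 against 70/10/20, an excess in the worst grade drawn mainly from the middle one: 75% against 18% to 19%. A large loss.
- Ease 90/8/2 against 85/11/4, a small shift: both below 15%, so the choice matters little.

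**The case against.** The strongest reply has three parts.

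First, the assignment is inferred. The article does not say that the graded outcomes go to chi-squared or Fisher, the Mann-Whitney test is already in the plan, and mapping each variable to a test is often left to a fuller document. This limits how firmly the point can be put. It does not remove it, because the article states a rule rather than staying silent, and under that rule the rank test belongs to the continuous class.

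Second, chi-squared is a defensible choice. It responds to any pattern, and step 5 of the check shows a case in which a rank test would miss most of an excess of the worst grade. This stands: the change has a real, if limited, cost.

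Third, these are unpowered secondary outcomes and the named tests hold their error rate. This stands too.

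A reader might go further in three ways that the document does not support.
- One might include the number of insertion attempts. That is a count, and nothing in the article keeps it from the Mann-Whitney test.
- One might say that all the affected outcomes lie at the centre of the trial's question. Only ease of insertion matches the hypothesis; sore throat is one item in a list of complications.
- One might say that the weaker test tilts the trial towards its hoped-for conclusion. Non-inferiority is to be judged by the confidence interval for leak pressure against the 1.5 margin, which this point does not touch. Nor would a non-significant result on ease show that ease is preserved, whichever test is used.

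**Conclusion.** The point holds as a minor matter of efficiency. As most naturally read, the two-class rule analyses three ordered outcomes (ease of insertion, ease of mask bagging, sore-throat grade) with valid tests that discard their order. If the arms differ by a consistent shift across grades, the cost is about 6 to 11 points of power for three grades and 13 to 19 points for four. These sizes depend on assumed category rates and odds ratios. With a non-monotone difference there is no gain, or a loss. The primary leak-pressure analysis, its margin and the 58 or 64 per arm are unaffected.

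**What to change.** In the Statistical analysis section, state that ease of insertion, ease of mask bagging and sore-throat grade are ordinal. Compare each between arms by the tie-corrected Mann-Whitney test, or by a proportional-odds model giving a common odds ratio with 95% CI; choose one before the allocation code is joined to the data. Report the full table of counts and proportions by grade and arm for all three, and keep chi-squared or Fisher for yes/no outcomes such as first-attempt success.

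The cost is a sentence or two of text, with no new data and no change in sample size. The price is lower sensitivity to non-monotone differences, such as an excess of the difficult grade drawn mainly from the moderate one. The grade table keeps such a pattern visible even where the test does not detect it.

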## Discussion

Repeated and prolonged attempts of LMA insertion or reposition of a misplaced LMA may contribute to adverse respiratory events such as laryngospasm, hypoxemia, and pharyngeal mucosal injury. To improve the clinical performance of LMA insertion or to achieve optimal positioning, many factors affecting the LMA insertion should be evaluated and optimized. Of these, muscle relaxants have long been used with a belief that they can positively influence upper airway anatomy and ventilation efficacy. Contrary to this belief, it was reported that ventilation efficacy (represented by tidal volume and airway flow) and pharyngeal mucosal pressure were not altered after rocuronium administration [22, 23]. The increase in airway dilation after succinylcholine administration was temporary during initial pharyngeal fasciculation [22]. Nevertheless, some studies reported that muscle relaxants facilitated LMA insertion in anesthetized adult patients [8–10]. Since the pediatric airway differs anatomically from the airway of adults [4–7], LMA insertion in children can also differ from that in adults. Therefore, we designed this prospective, randomized, double-blind trial to evaluate the efficacy of muscle relaxants during the insertion of LMA in pediatric patients.

The sealing pressure of the LMA, or the OLP, is a marker of the pressure exerted by the cuff of the LMA against the pharyngeal mucosa. To avoid the risk of gastric insufflation and consequent gastric regurgitation, higher sealing pressure is the cornerstone of LMA use. In a previous study, a positive correlation was found between the OLP and the directly measured mucosal pressure [24]. Therefore, we thought that if muscle relaxants change the pharyngeal structures, they may also affect the OLP. Indeed, various studies have measured the OLP as a primary outcome to evaluate the efficacy of LMA insertion [25–27]. We also measure ease of insertion, insertion time for successful insertion, ventilator parameters, and fiberoptic bronchoscopy (FOB) view of the LMA to judge the quality of LMA insertion with or without muscle relaxants. To compare the residual effects of muscle paralysis and airway-related complications using muscle relaxants, we also check for postoperative respiratory adverse events such as desaturation, cough, stridor, laryngospasm, bronchospasm, and the degree of sore throat.

In pediatric anesthesia, the need for muscle relaxants has decreased with the development of new anesthetic agents and the pursuit of minimally invasive surgeries [13, 28]. If an adequate depth of anesthesia is maintained to suppress airway reflexes, movement, and hemodynamic response and to keep appropriate surgical conditions, an LMA can be maintained throughout an operation without administration of a muscle relaxant. Hence, we questioned whether muscle relaxants have beneficial effects on the clinical performance of LMA manipulation. To our knowledge, there is a lack of studies that investigate whether muscle relaxants yield any advantages on the clinical performance of LMA insertion and placement in pediatric patients under general anesthesia. If successful, this study will provide a resource to improve the process and safety of using pediatric LMAs under general anesthesia.

### Trial status

The recruitment commenced in April 2018 and aims to enroll 128 participants for the trial. It is anticipated that recruitment will end by April 2019.

## Abbreviations

BIS: Bispectral index
ET sevo %: End-tidal sevoflurane concentration
FLACC: Face, Legs, Activity, Cry, and Consolability
IQR: Interquartile range
IRB: Institutional Review Board
LMA: Laryngeal mask airway
mYPAS: Modified Yale Preoperative Anxiety Scale
OLP: Oropharyngeal leak pressure
PACU: Post-anesthesia care unit
PIP: Peak inspiratory pressure
TOF: Train of four
